## Abstract

**Introduction:**

Traumatic brain injury (TBI) is a major cause of disability, with annual global incidence estimated as 69 million people. Survivors can experience long-term visual changes, altered mental state, neurological deficits and long-term effects that may be associated with mental illness. TBI is prevalent in military personnel due to gunshot wounds, and blast injury. This study aims to evaluate the relationship between evolving visual, biochemical and mental health changes in both military veterans and civilians, suffering from TBI, and detect preliminary indicators of prognosis for TBI recovery, and quality-of-life outcomes.

**Methods and analysis:**

UNTANGLE is a 24-month prospective observational pilot study recruiting three patient groups: civilians with acute moderate-severe TBI, military veterans with diagnosis of a previous TBI and a control group of civilians or veterans with no history of a previous TBI. Patients will undergo visual, biochemical and mental health assessments, as well as patient-reported quality of life outcome measures over the course of a 1-year follow-up period.

**Ethics and dissemination:**

Ethical approval has been obtained from the Health Research Authority and Health and Care Research Wales with a REC reference number of 23/NW/0203. The results of the study will be presented at scientific meetings and published in peer-reviewed journals, including both civilian and military-related publications. We will also present our findings at national and international meetings of learnt neuroscience and neuropsychiatry and military societies. We anticipate that our pilot study will inform a larger study on the long-term outcomes of TBI and quality of life, specific to military veterans, such that potential interventions may be accessed as quickly as possible.

**Trial registration number:**

ISRCTN13276511https://doi.org/10.1186/ISRCTN13276511.

STRENGTHS AND LIMITATIONS OF THIS STUDYThis is a prospective study measuring visual and serum biomarkers, mental health and quality of life symptoms within two different cohorts of traumatic brain injury (TBI) patients (acute TBI in civilians and in veterans with a diagnosis of previous TBI) for comparison.Inclusion of an acute civilian TBI group will ensure that we will be able to capture patients within 14 days after a TBI, meaning that early predictors and pathogenic events will be captured.Veterans may only be included in the study some months after the TBI, due to access to this population, possibly introducing confounding variables.As a pilot study, the number of participants in each group will be small, limiting the generalisability of the results. Nonetheless, our pilot study will generate critical data for the design and sample size estimations of future trials.

## Introduction

Head injury is the most common cause of death and disability in people <40 years old in the UK, with 1.4 million people a year attending emergency departments in England and Wales, and about 200 000 people requiring hospital admission.^1^ Five per cent of injuries are moderate to severe traumatic brain injury (TBI), which can have fatal outcomes and long-term disability. The most common cause of the injury in the elderly is falls in contrast to road traffic collisions in the young.^2^ TBI, whether mild (mTBI) or severe (sTBI) results in neurological deficits as well as altered cognitive or mental state, contributing to the increase in mental health disorders that are seen post-TBI.^3 4^ For example, depression,^4^,^8^ obsessive compulsive disorders,^9^,^13^ post-traumatic stress disorder (PTSD) and post-traumatic amnesia,^14^,^16^ psychosis,^8^ and personality changes such as apathy^7^ and aggression^8^ can occur after TBI, and increases the burden of living with TBI.^14^

According to the TRACK-TBI study, one in five individuals experience a mental health disorder after mTBI,^14 16^ and the rates of completed suicide after TBI were almost three times the general population in these patients.^16^ TBI is a particular concern in military personnel, exposed to events such as gunshot wounds or explosive blast injury. Of military personnel returning from Iraq and/or Afghanistan, up to 40% of personnel in the USA had a mTBI,^17^ and 25% in the UK cohort,^18^ with one report suggesting that mental health and neurological disorders could affect as many as 70% of veterans.^19^ Individuals sustaining TBI can also develop optic nerve, tract, radiation or occipital lobe damage that manifest as colour vision, stereopsis and visual field defects, with corresponding retinal changes detected by optical coherence tomography (OCT).^20^,^24^

Up to 80% of TBI patients suffer visual disturbances. Given that structural changes to the optic nerve manifest post-TBI, including in subclinical patients, it is possible that changes in visual structure and function may have future uses in diagnosis and prognostication of TBI, as well as being important to the patient’s function and well-being.^20 25^ It is recognised that individuals with visual impairment are at greater risk of developing mental health problems such as depression and anxiety.^26^ For example, nearly one-third of individuals with visual impairment experienced mild depressive symptoms, while 10%–45% of people reported moderate to severe depressive symptoms,^27^,^29^ and since vision loss is treated as a physical condition, the psychological impact is often under-recognised.^30^

Since there is an overlap between brain injury and mental health disorders, which may occur after damage to neuronal pathways, TBI fluid and imaging biomarkers may have diagnostic and prognostic value for TBI severity and mental health outcomes. For example, the fluid biomarkers glial fibrillary acidic protein (GFAP), S100β, tumour necrosis factor-α and myelin basic protein are associated with TBI severity, and have been suggested as biomarkers of mental health disorders with poor prognosis.^31^

Currently, TBI treatments are limited, and long-term interventions are symptomatic. Therefore, a better understanding of the neuropsychiatric changes caused by TBI, through longitudinal monitoring of biofluids and visual function along with patient-reported quality of life measures in acute TBI patients and military veterans with TBI, could provide insights into potential preventative treatments after TBI and possible disease-specific and transdiagnostic discovery bioscience with significant and wider impact. The study could therefore inform the design of a much-needed larger clinical trial in this patient population.

### Study hypotheses

TBI-induced alterations in brain structure are associated with the risk of subsequent mental health disorder.TBI-induced changes can be detected using fluid and imaging biomarkers.TBI-induced changes in biomarkers may identify those at risk of poor recovery and the development of mental health conditions affecting the quality of life.Changes in visual structure and function predict mental health and quality of life and associate with TBI-related biomarkers.

#### Study aims

To conduct a pilot study on the long-term outcomes of TBI and correlate this with candidate biomarkers in blood and saliva from veterans and non-veterans with TBI alongside measures of quality-of-life measures such as visual and mental health assessments and patient-reported outcome measures (PROMs). Through these multidimensional assessments, the study aims to better understand the relationship between the different long-term manifestations of TBI and how quality of life is affected by the injury.

### Methods and analysis

#### Overall study design

This is a single centre prospective observational pilot study in three groups of 30 participants each: civilians admitted to the Queen Elizabeth Hospital (QEH) in Birmingham with acute moderate-severe TBI, military veterans with diagnosis of a previous TBI and a control group of civilians or veterans with no history of TBI. Patients will undergo visual, biochemical and mental health assessments, as well as patient-reported symptoms and quality of life outcome measures over the course of a 1-year follow-up period (see figure 1 for overview).

**Figure 1 F1:**
[figure not shown]
Biofluids, visual, psychiatric assessments and PROMs timeline. PROMs, patient-reported outcome measures; TBI, traumatic brain injury.

In the acute TBI group (predictive group), biofluid collection, visual function, depression, anxiety, PTSD, suicidal behaviour, alcohol use and quality of life data through patient-reported outcome measures (PROMs) will be collected within 14 days after TBI. The same tests will be repeated in outpatients at 6- and 12 months after enrolment. At 1 month after enrolment, biofluid collection, psychiatric symptoms and quality of life outcomes will be repeated to monitor the recovery trajectory. PROMs will be completed remotely by each participant every 3 months for the 12-month follow-up period.

Veterans will also have biofluids collected, visual function and psychiatric assessments and quality of life measures collected using PROMs at enrolment and at 6- and 12-month follow-up. PROMs will also be completed remotely by participants every 3 months.

Control participants will be age and gender-matched to the acute TBI group and recruited from both civilian and veterans cohorts with no TBI history. They will have biofluids collected, visual function and psychiatric assessments and quality of life measures collected via PROMs at enrolment and at 6 months only (see tables1^3^ for planned assessment schedules in the three participant groups).

**Table 1 T1:** Assessments delivered within the trial period for acute traumatic brain injury patient group

	Trial period			
	Enrolment	Initial assessment (may be at enrolment)	Postallocation (monitoring interval clinically determined)	Close-out
Timepoint	−t_1_	Contact 1 (0–14 days post head injury or at enrolment)	Contact 2–5 (1, 3, 6 and 9 months after head injury or enrolment)	Contact 6 (12 months after head injury)
Enrolment				
Eligibility screen	X			
Informed consent	X			
Assessments				
Collect blood and saliva		X(face to face)	X(1 and 6 months only, face to face)	X(face to face)
Visual function tests (visual acuity, visual field, optical coherence tomography (OCT), OCT angiography, pupillometry, saccadic latency, autorefraction, colour vision and contrast sensitivity)		X(face to face)	X(1 and 6 months only, face to face)	X(face to face)
Social and occupational functioning assessment		X(face to face)	X(1 and 6 months only, face to face)	X(face to face)
Self-reported outcomes measures collected by post or electronically (eg, BIVSS visual impairment, PHQ-9, GAD-7, PCL-5, SBQ-R, AUDIT and EQ-5D-5L)		X(all collected remotely)	X(1, 3, 6 and 9 months, all collected remotely)	X(all collected remotely)
Head injury outcome				X

AUDITAlcohol Use Disorders Identification TestBIVSSBrain Injury Vision Symptom SurveyEQ-5D-5LEuroQol 5-Dimension 5-Level (Quality of Life)GAD-7General Anxiety Disorder-7PCL-5Post-Traumatic Stress Disorder Checklist for DSM-5PHQ-9Patient Health Questionnaire-9SBQ-RSuicidal Behaviour Questionnaire Revised

**Table 2 T2:** Assessments delivered within the trial period for the veteran’s participant group

	Trial period			
	Enrolment	Initial assessment (may be at enrolment)	Postallocation (monitoring interval clinically determined)	Close-out
Timepoint	−t_1_	Contact 1 (at enrolment)	Contact 2–4 (3, 6 and 9 months after enrolment)	Contact 5 (12 months after head injury)
Enrolment				
Eligibility screen	X			
Informed consent	X			
Assessments				
Collect blood and saliva		X(face to face)	X(at 6 months only, face to face)	X(face to face)
Visual function tests (visual acuity, visual field, optical coherence tomography (OCT), OCT angiography, pupillometry, saccadic latency, autorefraction, colour vision and contrast sensitivity)		X(face to face)	X(at 6 months only, face to face)	X(face to face)
Social and occupational functioning assessment		X(face to face)	X(at 6 months only, face to face)	X(face to face)
Self-reported outcomes measures collected by post or electronically (BIVSS visual impairment, PHQ-9, GAD-7, PLC-5, SBQ-R, AUDIT and EQ-5D-5L)		X(all collected remotely)	X(at 3, 6 and 9 months, all collected remotely)	X(all collected remotely)
Head injury outcome				X

AUDITAlcohol Use Disorders Identification TestBIVSSBrain Injury Vision Symptom SurveyEQ-5D-5LEuroQol 5-Dimension 5-Level (Quality of Life)GAD-7General Anxiety Disorder-7PCL-5Post-Traumatic Stress Disorder Checklist for DSM-5PHQ-9Patient Health Questionnaire-9SBQ-RSuicidal Behaviour Questionnaire Revised

**Table 3 T3:** Assessments delivered within the trial period for healthy control group

	Trial period	
	Initial assessment (may be at enrolment)	Postallocation (monitoring interval clinically determined)
Timepoint	Contact 1 (single assessment point)	Contact 2 (6 months after enrolment)
Enrolment		
Eligibility screen	X	
Informed consent	X	
Assessments		
Collect blood and saliva	X(face to face)	X(face to face)
Visual function tests (visual acuity, visual field, optical coherence tomography (OCT), OCT angiography, pupillometry, saccadic latency, autorefraction, colour vision and contrast sensitivity)	X(face to face)	X(face to face)
Social and occupational functioning assessment	X(face to face)	X(face to face)
Self-reported outcomes measures collected by post (BIVSS visual impairment, PHQ-9, GAD-7, PLC-5, SBQ-R, AUDIT and EQ-5D-5L)	X(all collected remotely)	X(6 months, all collected remotely)
Head injury outcome	N/A	

AUDITAlcohol Use Disorders Identification TestBIVSSBrain Injury Vision Symptom SurveyEQ-5D-5LEuroQol 5-Dimension 5-Level (Quality of Life)GAD-7General Anxiety Disorder-7PCL-5Post-Traumatic Stress Disorder Checklist for DSM-5PHQ-9Patient Health Questionnaire-9SBQ-RSuicidal Behaviour Questionnaire Revised

The acute TBI cohort will enable us to investigate changes related to recent TBI. This will be investigated only within the civilian patients due to the restricted access to military personnel sustaining recent TBI. Veterans cohort will be included within the study, enabling investigating the longer-term effects on TBI. We, accordingly, will be able to evaluate findings in participants with TBI history against the control group over a long-period of time.

The study opened recruitment in December 2023 and based on the current recruitment pace, we estimate that the last participant will continue until December 2025.

#### Eligibility and exclusion criteria

To be included in the study, participants are required to be over 18 years old, have two eyes and must have sustained TBI. Control participants should not have a diagnosis or history of moderate or severe TBI. Exclusion criteria for all three groups include: participants below 18 years old, are pregnant, have pre-existing neuropsychiatric conditions, retinal or optic nerve disorder or are registered as sight impaired.

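### The control group is defined two ways: no TBI history in the design text, but only no moderate or severe TBI in the eligibility criteria

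*Protocol article*

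**What the plan says.** The protocol article defines the control group in four places.

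- Abstract, Methods and analysis: "a control group of civilians or veterans with no history of a previous TBI".
- Overall study design, opening paragraph: "a control group of civilians or veterans with no history of TBI".
- Overall study design, paragraph on control participants: "recruited from both civilian and veterans cohorts with no TBI history".
- Eligibility and exclusion criteria: "Control participants should not have a diagnosis or history of moderate or severe TBI".

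The first three set no severity limit. The fourth does, and the exclusions that follow it for all groups (age, pregnancy, prior neuropsychiatric conditions, retinal or optic nerve disorder, registered sight impairment) do not mention mild TBI.

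On the case side, the acute group is described in Overall study design as civilians "with acute moderate-severe TBI". The veteran TBI group needs a diagnosis of an earlier TBI, with no severity given. The eligibility section pools the requirement into one sentence: "participants are required to be over 18 years old, have two eyes and must have sustained TBI".

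The Introduction treats mild TBI as an injury with consequences. It says neurological deficits and altered mental state follow mild as well as severe TBI, and reports that among personnel returning from Iraq and/or Afghanistan "up to 40% of personnel in the USA had a mTBI", against 25% in a UK cohort.

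**The concern.** Eligibility criteria are what a recruiter applies. If the eligibility sentence is the one used, a volunteer with a past concussion or mild blast injury is accepted as a control, although three other statements in the same article say that person should not be there.

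Controls are recruited partly from veterans, the population in which the article itself says mild TBI is common. The veteran TBI group has no severity floor, so the same history could place a veteran on either side of the comparison.

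The between-group comparisons are at stake. The text after Table 3 says findings in people with a TBI history will be set against the controls, and Statistical methods plans group comparisons of biomarkers and of mental health and quality-of-life outcomes. If mild TBI moves these measures in the same direction as the case injuries, exposed controls pull the reference mean toward the cases and the differences shrink. The strengths and limitations box says the pilot will feed the sample size estimates of future trials, so a diluted difference would carry forward.

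**Working it through.** **Step 1: apply the rules to one person.** Take a veteran with one diagnosed mild TBI and none of the listed exclusions.

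| Rule | Outcome |
|---|---|
| Control, by Abstract and Overall study design (no TBI history) | Not eligible |
| Control, by Eligibility and exclusion criteria (moderate or severe TBI barred) | Not barred |
| Veteran TBI group, by Overall study design (diagnosed earlier TBI, any severity) | Eligible |

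The first two rows give opposite answers, so this is a contradiction and not an omission. The second and third rows together show the overlap between case and control groups.

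**Step 2: illustrate the size.** The protocol gives no figure for this, so there is none to reproduce. Inputs:

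- controls recruited: 30 (Overall study design);
- mild TBI rate in veterans: 25%, the UK figure (Introduction);
- veteran share of controls, v: not stated; 50% assumed, with 25% and 100% shown as a range;
- mild TBI among civilian controls: not stated; zero assumed;
- mild-TBI effect as a fraction of the case effect, c: not stated; 0.5 to 1.0 assumed.

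Exposed controls = 30 × v × 0.25. Exposed share f = v × 0.25.

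If cases differ from unexposed controls by D, exposed controls are shifted by cD and the control mean moves by f × c × D. The expected contrast is then D × (1 − f × c), and the proportional attenuation is f × c.

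| v | Exposed controls | f | Attenuation, c = 0.5 | Attenuation, c = 1.0 |
|---|---|---|---|---|
| 25% | 30 × 0.25 × 0.25 = 1.9 | 0.0625 | 3.1% | 6.25% |
| 50% | 30 × 0.50 × 0.25 = 3.75 | 0.125 | 6.25% | 12.5% |
| 100% | 30 × 1.00 × 0.25 = 7.5 | 0.25 | 12.5% | 25% |

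The last row is only an outer bound, because controls are to come from both civilians and veterans. If the design definition is applied in practice, f = 0 and the attenuation is zero.

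**Step 3: put it on a scale the protocol uses.** Statistical methods cites a 5 µm difference in retinal nerve fibre layer thickness between boxers and controls. In the 50% row, a true difference of that size would be expected to appear as 5 × (1 − 0.0625) = 4.69 µm or 5 × (1 − 0.125) = 4.38 µm.

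**Step 4: what is not affected.** The power statement concerns change in this thickness between correlated repeated measures. Within-group change over time, and biomarker–outcome associations within the TBI groups, do not use the controls.

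**The case against.** The strongest reply is that three consistent statements outweigh one loose sentence. If staff screen for no TBI history, no exposed control is enrolled and nothing is lost. That is possible, and zero belongs in the range. It does not remove the conflict: the odd sentence sits in the eligibility section, and the article does not say which statement governs.

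The second reply is that the illustration rests on weak inputs. The 25% concerns personnel returning from two conflicts, not all veterans. The veteran share of controls is unknown. The exclusions for neuropsychiatric and for retinal or optic nerve disease would remove some of the mildly injured people whose results would distort the contrasts. An effect of 100% is hard to defend against acute moderate-severe injury, though less so against a veteran group with no severity floor. In the other direction, setting civilian mild TBI to zero understates exposure. All of this stands, so the figures show an order of magnitude and are not an estimate.

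Three stronger readings are tempting, and the document does not support them.

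- **That mild acute TBI is also admitted.** The eligibility phrase "have two eyes and must have sustained TBI" carries no severity, but the Abstract and Overall study design both say moderate-severe, and Overall study design gives the 14-day window. The pooled sentence also covers the veteran group, and read literally would require TBI of the controls. It is condensed wording, not an opposing rule.
- **That attenuation reaches 20% with half the controls veterans.** That needs the US figure, which is itself an upper limit (0.50 × 0.40 × 1.0 = 20%). The study is single-centre in Birmingham and recruits veterans through charities and organisations that include UK ones.
- **That every analysis is compromised.** Within-group analyses are not.

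Finally, this is a pilot with 30 per group that admits limited generalisability. That limits the consequences, but not the need for a single definition of the reference group.

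**Conclusion.** The point holds for the control definition. The article states two incompatible rules, and the one in the eligibility section admits mild TBI to the reference group and lets a veteran with diagnosed mild TBI qualify as either case or control. The likely direction is toward smaller between-group differences, provided mild TBI acts in the same direction as the case injuries.

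The size cannot be computed from the document. With 25% mild TBI among veteran controls, half of the controls veterans, none exposed among civilians, and a mild-TBI effect of 50 to 100% of the case effect, about 4 of 30 controls are exposed and the attenuation is about 6 to 12.5%. Only the 25% and the 30 come from the protocol; the rest is assumed. A reader might infer that the acute group is diluted as well, or that the study's change analyses are biased. Neither follows from the text.

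**What to change.** Reconcile the Eligibility and exclusion criteria section with the Abstract and Overall study design, so that controls have no diagnosis or history of TBI of any severity, with mild TBI named explicitly.

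Because recruitment opened in December 2023, some controls may already have been enrolled under the looser wording. Ask each enrolled control about past mild TBI, record the answer, and report the between-group analyses with and without any who report it. Add the same question to screening.

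As minor alignment in the same edit, repeat in the eligibility section the acute-group severity already stated elsewhere, and say that the requirement to have sustained TBI does not apply to controls.

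The cost is a short amendment during recruitment, one screening question, contact with controls already enrolled, and somewhat slower recruitment of veteran controls. The sensitivity analysis will have fewer controls, and so less precision, if any are set aside.

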#### Statistical methods

Analyses will include all available data of recruited patients (not restricted to patients with complete follow-up). Between group comparisons will evaluate susceptibility to poor mental health and quality of life outcomes. Longitudinal data may show the latency of onset of mental health and quality of life problems after acute TBI, in order to time future interventions.

Candidate serum and visual biomarkers will be compared between groups and associated with mental health and quality of life outcomes to look for predictive value. Many of these data are continuous and normally distributed and repeated measures data (including data from both right and left eyes). As such, generalised estimating equations will be used to determine changes over time with data from each eye and different time points treated as repeated measures, with a binomial distribution used for binary and ordinal outcomes as appropriate. Trial statisticians in the Birmingham Clinical Trials Team will be engaged for further statistical advice, if required.

This is a pilot study to evaluate longitudinal changes in fluid and visual biomarkers of brain injury, mental health status and self-reported quality of life measures in patients with TBI (civilian and military veterans). As such, sample size is based on:

Statistical advice that in a pilot/feasibility study, 30 subjects in each group are recommended to allow estimation of the parameters of interest.Childs *et al*^36^ who showed a difference of 5 µm in global retinal nerve fibre layer (RNFL) thickness between boxers and controls, an average RNFL thickness of 101 and an SE of 1.8.

Past experience in the concussion clinic suggests that we can follow 80% of patients at the 3-month point (ie, only 20% lost to follow-up). We powered the study to detect a 5 µm change in the RNFL thickness, assuming a correlation of 0.9 between repeated measures (conservative given that in the absence of pathology, RNFL thickness varies very little). Simulated power calculations in R revealed that 24 participants with complete data (recruiting 30 and assuming a 20% drop out) would have >80% power to detect a 2 µm change in RNFL thickness and 100% power to detect a 5 µm decrease.

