### Consent

Within both veteran and control groups, participants should have capacity to consent and be willing and able to follow the protocol, except for the acute TBI cohort, who may not have capacity to consent as a result of TBI. Written consent will be obtained by the local research team, which may include the site principal investigator, co-investigators or research assistants. Veterans will be recruited through veteran charities such as Bravo Victor, Blind Veterans UK or other veterans charities and organisations. In the acute TBI groups attending the QEH in Birmingham for head injury, identified participants may not have the capacity to consent and as such, written consultation will be obtained from a personal (ie, relative) or nominated (professional) consultee. However, if a patient regains consciousness and capacity, their consultee will be notified, and the patient will be given the opportunity to provide written consent to remain in the study or withdraw. Unconscious patients will only have blood collected and OCT scans conducted as all other tests require a patient to be conscious and have capacity to complete. The willingness of participants to remain in the study will be re-affirmed at each study visit with the patient or consultee as appropriate. Patients have the right to withdraw from the study at any time, but all data collected will be retained and used in the analysis to avoid bias in assessment of outcomes.

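### Eyes injured directly in the same trauma are neither clearly excluded nor separated in the analysis, which can bias group comparisons and vision-outcome associations read as TBI-induced

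*Protocol article*

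**What the plan says.** Under Eligibility and exclusion criteria, participants in the TBI groups must "have two eyes and must have sustained TBI". For all three groups the exclusions include being under 18, being pregnant, and participants who "have pre-existing neuropsychiatric conditions, retinal or optic nerve disorder or are registered as sight impaired". Neither sentence mentions injury to the eye or orbit from the trauma that caused the TBI.

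Under Statistical methods, candidate visual biomarkers are to be compared between groups and related to mental health and quality of life. Generalised estimating equations (GEE) are to be used with "data from each eye and different time points treated as repeated measures". No term, stratum or repeat analysis is named for an eye that was itself injured.

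Two of the Study hypotheses carry the interpretation: "TBI-induced changes can be detected using fluid and imaging biomarkers", and "Changes in visual structure and function predict mental health and quality of life and associate with TBI-related biomarkers". In the acute group the first visual data "will be collected within 14 days after TBI", so there is no pre-injury measurement. The Introduction names falls and road collisions as common causes, and describes military personnel as "exposed to events such as gunshot wounds or explosive blast injury". Under Consent: "Veterans will be recruited through veteran charities such as Bravo Victor, Blind Veterans UK or other veterans charities and organisations".

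**The concern.** Falls, collisions, gunshots and blasts can injure the eye or orbit as well as the brain. An eye with a damaged lens or pupil sphincter can give abnormal acuity, contrast, field, pupillometry or autorefraction results without any contribution from the brain. Under the stated rules such an eye enters the TBI groups as an ordinary observation. Controls are not selected on a head trauma, so they would not be expected to carry such eyes at the same rate, and the imbalance runs mainly one way.

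What is at stake is attribution. A difference between TBI participants and controls, or an association between poor vision and poor mental health, would be described as TBI-induced when part of it comes from local eye damage. With 30 participants per group, a handful of eyes can matter. Study limitations names varying time since TBI in veterans as a confounder, but not this.

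**Working it through.** **1. What the exclusion removes, by reading.** The ocular item can be read in three ways.

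- (a) *Pre-existing* governs it and means before the injury. Retinal or optic nerve damage from the same trauma is then admitted.
- (b) *Pre-existing* governs it and means before enrolment. A veteran with a known traumatic retinal or optic nerve disorder is excluded, because the trauma precedes enrolment. An acute patient is excluded if the disorder is known by enrolment.
- (c) *Pre-existing* does not govern it. Any retinal or optic nerve disorder is excluded in all groups.

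Under (b) and (c) the criterion may also remove optic nerve and retinal damage of the kind that the Introduction describes as a consequence of TBI and that the hypotheses set out to detect. Under all three, injury to lens, pupil or orbit that spares retina and nerve is admitted. Sight-impairment registration is a status of the person, whereas the analysis is by eye, so it does not screen single eyes.

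**2. Which analyses are exposed.** Let a share *f* of a group's eyes carry an offset *d* from direct injury.

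- Between-group mean at any visit: shifted by *f × d*.
- Within-person change with a stable offset: (y₂ + d) − (y₁ + d) = y₂ − y₁, so no shift.
- Within-person change when the offset moves from d₁ to d₂ through healing or progression: shifted by *f × (d₂ − d₁)*.
- Association with outcome: affected if *d* is related to outcome by a route other than brain injury.

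**3. The plan's own figures.** Recruiting 30 with 20% dropout gives 30 × 0.8 = 24, as stated. The stated power is for a within-person RNFL change: above 80% for 2 µm and 100% for 5 µm. For a paired t-test with n = 24, two-sided 5% (assumed, as no level is stated), the SD of change is SD × √(2 × (1 − 0.9)) = 0.447 × SD. The article gives a standard error of 1.8 but not the source study's group size *m*, so SD = 1.8 × √m is not fixed.

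- 5 µm: 98% or more for *m* from 10 to 50, consistent with the text.
- 2 µm: 96% at m = 10, 85% at m = 15, 78% at m = 18, 57% at m = 30. The claim of above 80% needs an SD of about 7.5 µm or less.

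The 2 µm figure therefore cannot be confirmed or refuted. The present point does not depend on it.

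**4. Illustrative size.** The documents give neither *f* nor *d*; all values here are assumptions.

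| Share of eyes *f* | RNFL shift for d = 10 to 20 µm |
|---|---|
| 5% | 0.5 to 1.0 µm |
| 10% | 1.0 to 2.0 µm |
| 20% | 2.0 to 4.0 µm |

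These RNFL rows apply only where such eyes are not already removed by the retinal or optic nerve exclusion.

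For acuity, take 3 of 60 eyes (30 participants × 2) worse by 1.0 logMAR, with an SD of 0.10 otherwise. The mean shift is 3/60 × 1.0 = 0.05. The SD becomes √(0.10² + 0.05 × 0.95 × 1.0²) = √0.0575 = 0.24.

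**The case against.** A reader might infer that direct eye damage is counted as TBI-induced visual and retinal change at every visit in both TBI groups. The documents do not support that. Retinal or optic nerve disorder is an exclusion in all three groups, and for veterans, whose trauma precedes enrolment, a known traumatic disorder is most clearly screened out. A lasting RNFL deficit of 10–20 µm would itself look like a retinal or optic nerve disorder. These objections stand, and they confine the OCT part mainly to the acute group.

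A reader might also set the shifts above against the 2 and 5 µm in the power statement. Those are within-person changes, from which a stable deficit present at contact 1 largely cancels. This also stands: the scale is useful, but it is not a like-for-like benchmark.

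Next, the predictive aim in the fourth hypothesis does not need vision loss to run through the brain; the Introduction itself says that visual impairment raises the risk of depression and anxiety. That is fair. The bias concerns attribution to TBI, not prediction as such. That eye damage and brain injury are severe together is plausible, but the documents do not say so.

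Finally, the criteria are introduced as a list that may not be complete, in an article that condenses a fuller protocol, and treating both eyes as repeated measures in GEE is standard. If the full protocol has a criterion for direct eye injury, the sponsor can cite it. But the ambiguity of *pre-existing* is in the text as published, and GEE handles the correlation between eyes, not a systematic offset in some of them.

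**Conclusion.** The point holds in a limited form. As written, the criteria admit eyes with lens, pupil, orbital and some globe injury from the same trauma, and leave the status of traumatic retinal or optic nerve damage unclear. The analysis then pools these eyes without distinction. Between-group comparisons and vision-outcome associations are exposed, chiefly for acuity, contrast, field, pupil and accommodation, and in the acute group possibly for OCT. Within-person change is exposed only through healing or progression of the eye injury.

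The size cannot be established. The illustrative shifts show that a small share of eyes could matter in groups of 30; they do not show that it will. The conclusion assumes that some participants have direct eye or orbital injury, which the named mechanisms make plausible, and that the full protocol adds no further criterion.

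**What to change.** 1. State whether *pre-existing* governs the retinal and optic nerve item, and whether it dates from the injury or from enrolment. Reconcile this with the aim of detecting TBI-related optic nerve and retinal change.
2. At contact 1, flag each eye for direct ocular or orbital injury, using the admission record and existing imaging in the acute group and history in veterans.
3. Repeat the planned eye-level group comparisons and vision-outcome associations with flagged eyes left out and fellow eyes kept. Report this as a sensitivity analysis beside the all-eyes result.

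Agreement between the two analyses should not be made a condition for calling a change TBI-induced: there is no obvious agreement criterion, and with 30 per group such a rule would be fragile.

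The cost is one form item per eye and one repeat of models already planned, with no new examination. For participants already enrolled, the flag can be completed from records. The second analysis has slightly fewer eyes, and these may come disproportionately from the most severe injuries, so it could weaken a genuine effect. In veterans the flag depends on recalled history. Both are reasons to present the second analysis beside the first and not in its place.
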